## Abstract

**Background:**

In compliance with national and international guidelines, non-pregnant women with cervical intraepithelial neoplasia grade 3 should be treated by cervical conization. According to the definition of the large loop excision of the transformation zone (LLETZ) operation, the lesion needs to be resected, including the transformation zone. It is well known from the literature that the cone size directly correlates with the risk of preterm delivery in the course of a future pregnancy. Thus, it would be highly desirable to keep the cone dimension as small as possible while maintaining the same level of oncological safety.

**Methods/Design:**

The aim of this study is to analyze whether resection of the lesion only, without additional excision of the transformation zone, is equally as effective as the classical LLETZ operation regarding oncological outcome. We are performing this prospective, patient-blinded multicenter trial by randomly assigning women who need to undergo a LLETZ operation for cervical intraepithelial neoplasia grade 3 to either of the following two groups at a ratio of 1:1: (1) additional resection of the transformation zone or (2) resection of the lesion only. To evaluate equal oncological outcome, we are performing human papillomavirus (HPV) tests 6 and 12 months postoperatively. The study is designed to consider the lesion-only operation as oncologically not inferior if the rate of HPV high-risk test results is not higher than 5 % compared with the HPV high-risk rate of women undergoing the classical LLETZ operation.

**Discussion:**

In case that non-inferiority of the “lesion-only” method can be demonstrated, this operation should eventually become standard treatment for all women at childbearing age due to the reduction in risk of preterm delivery.

**Trial registration:**

German Clinical Trials Register (DRKS) Identifier: DRKS00006169. Date of registration: 30 July 2014.

## Background

Cervical cancer is the third most common cancer diagnosis and the fourth-leading cause of death in women worldwide, responsible for 9 % (529,800) of all new cancer cases and 8 % (275,100) of deaths caused by cancer in women in 2008 [1].

Precursor lesions of squamous cell carcinoma of the cervix uteri, which represent about 80 % of cervical cancers, are referred to as *cervical intraepithelial neoplasia* (CIN), which is distinguished in three degrees of severity (CIN 1 to 3) [2]. Compared with invasive cervical cancer, the occurrence of precancerous lesions of the cervix uteri is much higher.

A prerequisite for the development of cervical dysplasia is a persistent infection with high-risk human papillomavirus (HPV) types [3]. Anogenital HPV infection is a common sexually transmitted disease, estimated to affect 75 % to 80 % of sexually active adults younger than age 50 years [4]. The majority of HPV infections are self-limiting within 1 to 2 years [5]. These high-risk HPV types, particularly HPV 16 and 18, are responsible for the vast majority of cervical cancers [6], whereas low-risk HPV types are associated with condylomata acuminata.

HPV infections affect undifferentiated basal cells of the cervical epithelium within the transformation zone. The transformation zone is the area of the cervix where the columnar epithelium of the endocervix meets the squamous epithelium of the ectocervix.

Before puberty, the squamocolumnar junction lies within the endocervical canal. Owing to hormonal changes during puberty, the columnar epithelium extends outward and the squamocolumnar junction moves onto the ectocervix. Under exposure to the acidic vaginal environment, columnar epithelium can undergo physiological metaplasia and transform into squamous epithelium. The new squamocolumnar junction is then closer to the endocervix compared with the original squamocolumnar junction, and the zone in between is called the *transformation zone* of the cervix. Recently, a hypothesis has been stated that cervical cancer emerges from a newly described embryological cell population. These so-called cuboid cells are located directly at the squamocolumnar junction [7].

In accordance with national and international guidelines [8], standard treatment of non-pregnant women diagnosed with CIN 3 is conization of the cervix. This procedure is also called *large loop excision of the transformation zone* (LLETZ). The rationale for the removal of the transformation zone in addition to the lesion itself is that both the precursor lesion and cervical cancer itself typically arise in the area of the transformation zone.

In addition to general complications such as intraoperative or postoperative bleeding, infection, pain and scarring, cervical conization is associated with a significantly high rate of cervical weakness and a consequent increase in miscarriages and premature birth rates in future pregnancies [9–12]. This is of special interest because patients diagnosed with cervical dysplasia are typically of childbearing age, with an average age of 30 years [13, 14]. It is well known that the risk of preterm birth is directly correlated with the size of the removed cone [15–17]. With knowledge of these serious complications, there is a worldwide trend aimed at reducing surgical radicalism by removing the dysplastic lesion only, without additional resection of the transformation zone.

In a large retrospective study of over 150,000 women treated for CIN 3 between 1958 and 2008, it has lately been shown that women who received treatment more recently were at greater risk of developing cervical cancer [18]. It is suggested that this observation directly correlates with the use of less aggressive treatment over the last two decades [19].

With awareness of this development, it is important to respecify the necessary extent of a conization. Primarily, the optimum cone size needs to guarantee the highest oncological safety defined by low recurrence and high R0 resection rates. Simultaneously, the extent of the resection should be as small as possible to reduce the morbidity risk during subsequent pregnancies.

The primary objective of the present study is therefore to compare the classical LLETZ operation (that is, resection of the lesion with entrainment of the transformation zone) with resection of the colposcopically abnormal lesion only in the light of oncological safety.

## Methods/Design

### Study design

The Evaluation of Clinical Outcome after Reduction of Conization Size (or ECO-ROCS) trial is a multicenter, prospective, parallel-group, patient-blinded, non-inferiority randomized controlled trial in which we are assessing oncological comparability of two conization procedures: (1) classical LLETZ, comprising excision of the dysplastic lesion, including resection of the transformation zone; and (2) excision of the dysplastic lesion only.

### Study setting

This study is being conducted in 13 study centers, all of which run a specialized dysplasia clinic (Munich (two), Hannover, Wolfsburg, Berlin, Kiel, Regensburg, Stralsund, Hamburg, Düsseldorf, Aachen, Ulm, Münster). The participating study centers and investigators are fully listed in the German Clinical Trials Register (DRKS00006169).

### Sample size and statistics

A sample size of 892 patients was calculated with the POWER procedure of SAS for Linux 9.3 software (SAS Institute, Cary, NC, USA) using the following parameters: non-inferiority margin of 5 %, α = 0.05, 80 % power and one-sided test. A rate of 90 % negative HPV test results 6 months after conization was taken as a reference [20] for both groups. Assuming a 10 % dropout rate, we aim for a sample size of 1000 patients.

The statistical inference regarding the primary outcome will be based on a one-sided 95 % confidence interval for the risk difference, calculated as the proportion of HPV-positive patients in the control group minus the corresponding proportion in the experimental group. If the upper limit of the confidence interval is less than the non-inferiority margin of minus 5 %, non-inferiority will be regarded as established.

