### Recruitment und randomization

Patients are being seen and diagnosed in specialized dysplasia outpatient clinics of the participating study centers. After they provide us their written informed consent, participants fulfilling all required inclusion and exclusion criteria are given a five-digit pseudonym (patient identifier), with the first two numbers indicating the study center and the latter three numbers indicating a sequential patient number. Patients are randomly assigned by their pseudonym with equal probability to either of the two treatment arms, using a 1:1 ratio. Randomization is carried out using the web-based Randoulette randomization service of the Institute for Medical Informatics, Biometry and Epidemiology, University of Munich, Germany. The platform offers a web-based form in which to enter patient identifier, sex, age and study center, as well as the strata of the patient. Access to the randomization service is provided to the two leading investigators at each study center. Patients are stratified by age (>30 or ≤30 years) and study center.

After the information is entered, the study arm is selected according to a predefined randomization scheme, in this case an unblended, stratified block randomization. To maintain allocation concealment, the exact length of blocks is kept secret by the Randoulette randomization service. The entered information, as well as the randomization results, are stored in the Randoulette database.

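### Randomisation is stratified by age and centre, but the primary risk difference is described without strata; stratifying it would be a cheap, minor gain

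*Protocol article*

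**What the plan says.** All references are to the Protocol article.

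- Recruitment und randomization: allocation is "with equal probability to either of the two treatment arms, using a 1:1 ratio", in stratified blocks of undisclosed length. "Patients are stratified by age (>30 or ≤30 years) and study center". Study setting lists 13 centres, so there are up to 2 × 13 = 26 cells.
- Sample size and statistics: the arms are compared on the risk difference, with a one-sided interval at the 95% level. The difference itself is described as "calculated as the proportion of HPV-positive patients in the control group minus the corresponding proportion in the experimental group". This section mentions no stratification factor and names no interval method.
- Same section: the sizing uses "non-inferiority margin of 5 %, α = 0.05, 80 % power and one-sided test". For the outcome, "A rate of 90 % negative HPV test results 6 months after conization was taken as a reference" in both groups. "A sample size of 892 patients was calculated with the POWER procedure of SAS", and then "Assuming a 10 % dropout rate, we aim for a sample size of 1000 patients".

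**The concern.** Stratified blocks balance the arms on age group and centre. If those factors predict a positive HPV test at 6 months, the difference between arms varies less from trial to trial than under simple randomisation. A standard error built from the two overall proportions does not reflect this, so the interval comes out a little too wide and the test a little conservative.

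The article gives reasons to think the factors could matter, but no sizes:

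- Additional investigations says that young patients in particular often carry several HPV types, so the conventional test can stay positive after the lesion-causing type has gone. That links age to the primary endpoint.
- The Discussion says that cone size differs between surgeons, and surgeons work within centres.

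At stake is a small amount of precision that the randomisation has already made available. The validity of the conclusion is not at stake.

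**Working it through.** **Inputs.** From Sample size and statistics: margin 5 points, one-sided α 0.05, power 80%, HPV-positive rate 10% in both arms, 892 evaluable patients (446 per arm). From Study setting and Recruitment und randomization: 13 centres × 2 age groups = 26 cells. Assumed: the standard deviation (SD) of the true HPV-positive rate across cells, because the documents give none. The intended criterion is used throughout: the upper limit for the excess in the lesion-only arm must be below 5 points. The sign of the written decision rule is a separate matter.

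**1. The plan's own figure.** The unstratified formula gives n per arm = (1.645 + 0.842)² × 2 × 0.10 × 0.90 / 0.05² = 445.1, rounded up to 446, or 892 in total. This matches. For dropout, 892 / 0.9 = 991.1, rounded up to 992; the article uses 1000.

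**2. Unstratified interval.** SE = √(2 × 0.09 / 446) = 2.009 points. The one-sided half-width is 1.645 × 2.009 = 3.30 points. Power = Φ(5/2.009 − 1.645) = 80.1%.

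**3. Stratified interval.** With the mean rate held at 10%, the average within-cell variance is 0.09 − SD². Hence SE_s = √(2 × (0.09 − SD²) / 446), and stratified power is Φ(5/SE_s − 1.645).

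The blocks also stabilise the crude estimate, so its true spread is close to SE_s even though its interval still uses 2.009. Its actual power is therefore Φ((5 − 3.304)/SE_s).

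| SD across cells (points) | Half-width, stratified | Shortened by | Power, crude | Power, stratified |
|---|---|---|---|---|
| 0 | 3.30 | 0 | 80.1% | 80.1% |
| 3 | 3.29 | 0.02 | 80.2% | 80.4% |
| 5 | 3.26 | 0.05 | 80.4% | 81.0% |
| 7 | 3.21 | 0.09 | 80.7% | 82.0% |
| 8 | 3.18 | 0.12 | 80.9% | 82.6% |
| 10 (as large as the mean rate) | 3.12 | 0.19 | 81.5% | 84.0% |

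**4. Simulation of power.** Settings: 892 patients, 26 cells, 10% mean positivity, crude Wald interval against a Mantel-Haenszel risk difference. Where two results are given, they come from separate runs.

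- No stratum effect: 80.0% crude against 79.9% to 80.0% stratified.
- Centre SD 0.6 on the logit scale and age odds ratio 2 (cell SD about 6 points): 80.0% against 80.9%, and 80.6% against 81.6%. Half-width 3.30 against 3.23.
- Centre SD 0.8 and age odds ratio 2.5 (cell SD about 8 points): 80.4% against 82.0%, and 81.2% against 82.7%. Half-width 3.30 against 3.18.

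These agree with the table.

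**5. False-positive rate at a true 5-point excess.** With balanced cells and stratum effects present, the crude rate was about 4.5% to 4.7% and the stratified rate about 5.0% to 5.2%. A further simulation with unequal cell sizes, an assumed block length of 4 and 4,000 runs per scenario gave 4.9% to 5.7% crude and 4.8% to 6.0% stratified, with a Monte Carlo error of about 0.35 points. Both methods stay near the nominal 5%.

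**6. Cell size.** 892 / 26 ≈ 34 patients per cell. At 10% positivity that is about 3 events.

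**The case against.** The strongest objection is that the article does not commit to a crude interval. The quoted clause mainly fixes the effect measure and its direction, no interval method is named, and a Mantel-Haenszel limit is also a confidence interval for a risk difference. Handling of strata is the kind of detail an article leaves to the full protocol or SAP. This stands in part. The only calculation described is a difference of overall proportions and the sizing is unstratified, but the full plan may already stratify. The recommendation is therefore conditional.

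Three stronger readings are tempting, and the documents do not support them:

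- A reader might infer that the unstratified interval is wrong. It is valid; ignoring prognostic strata can only make it somewhat wide.
- A reader might infer that the trial falls short of the power it was sized for. It does not: 892 was computed for an unstratified interval, and at a 10% mean rate that interval keeps at least the planned 80%. Stratifying adds a small bonus.
- A reader might infer from the remark on cone size that centre strongly predicts outcome. The remark describes variation in German practice, not HPV results, and the Surgery section prescribes the extent of resection in both arms.

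It might also be argued that dropout could unbalance the cells. Stratifying would correct imbalance in age and centre, but not dropout related to outcome within a cell. Nothing in the documents allows this to be sized.

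Finally, sparse cells make stratification less than free. This stands, and it is why a pooling rule belongs in the fix.

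**Conclusion.** The point holds as a minor efficiency improvement. The design stratifies by age and centre, and the primary risk difference as described does not. For an assumed SD across cells of up to about 8 points, stratifying gains about 0 to 2 points of power and 0 to 0.12 points of half-width. Only an SD as large as the mean rate itself takes the gain further, to about 2.5 points of power (84.0 − 81.5) and 0.19 points of half-width.

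The direction is certain. The size rests on assumed stratum effects, a 10% mean rate and near-balance within cells. Confidence that the final analysis is in fact unstratified is only moderate, because the article leaves the interval method open.

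**What to change.** Unless the full protocol or SAP already says so, add a short statement of the primary analysis. The one-sided 95% confidence limit is taken from a Mantel-Haenszel (or model-based standardised) risk difference stratified by age group and centre. Very small centres are pooled by a rule written down before outcome data are seen. The crude difference is reported as a sensitivity analysis.

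The cost is a sentence or two and a different procedure call. No design element or sample size changes. The one real burden is the pooling rule, needed because cells average about 34 patients and 3 events. If the strata prove unimportant, power is essentially unchanged.

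### The non-inferiority decision rule is reversed: as written, lesion-only surgery passes only if it is shown to be more than 5 points worse

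*Protocol article*

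**What the plan says.** All of the following is in the protocol article.

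- **Contrast** (Sample size and statistics): the risk difference is "the proportion of HPV-positive patients in the control group minus the corresponding proportion in the experimental group", with a one-sided 95% confidence interval.
- **Decision rule** (same paragraph): "If the upper limit of the confidence interval is less than the non-inferiority margin of minus 5" %, non-inferiority is taken as established.
- **Design inputs** (same section): "non-inferiority margin of 5" %, alpha 0.05, 80% "power and one-sided test", and 90% "negative HPV test results 6 months after conization was taken as a reference" for both groups. The result is 892 patients, raised to 1000 for dropout.
- **Abstract, Methods/Design**: lesion-only is considered not inferior "if the rate of HPV high-risk test results is not higher than 5" % compared with classical LLETZ.
- **Study design**: the experimental procedure is excision of the dysplastic lesion only; the comparator is classical LLETZ.

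**The concern.** HPV positivity is the unfavourable result. With control minus experimental, an excess of positives after lesion-only surgery makes the difference negative. A non-inferiority claim has to exclude an excess of 5 points or more, so the data must rule out differences at or below -5. That is a statement about the lower limit.

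The written rule puts the upper limit below -5 instead. It is met only when the entire interval lies on the inferior side of the margin. Applied literally, a trial with equal arms would fail and a clearly worse operation would pass. The stated 80% power belongs to the opposite rule.

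The stakes are high because this is the trial's confirmatory decision, and the abstract's Discussion says a positive result should make lesion-only excision the standard for women of childbearing age.

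**Working it through.** **Inputs.** Margin 5 points, one-sided alpha 0.05, power 80% and 90% HPV-negative (10% positive) in both arms come from Sample size and statistics. Allocation 1:1 comes from Recruitment und randomization. The article does not name the interval method, so a Wald interval is assumed here. This does not affect the direction of the error.

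**1. The plan's own figure.** For non-inferiority of two proportions with equal true rates:

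n per arm = (1.645 + 0.842)² × 2 × 0.9 × 0.1 / 0.05² = 445.1, rounded up to 446, so 892 in total.

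This matches the stated 892 exactly. With 10% dropout, 892 / 0.9 = 991.1, which fits the target of 1000. The sample size is therefore built for the conventional rule, and its inputs are sound.

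**2. The two rules.** Let D = positive(control) − positive(lesion-only), let e be the true excess in lesion-only, so D = −e, and let

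SE = √[0.1 × 0.9/446 + (0.1 + e)(0.9 − e)/446].

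- As written: D̂ + 1.645 SE < −0.05, with probability Φ((−0.05 + e)/SE − 1.645).
- Conventional: D̂ − 1.645 SE > −0.05, with probability Φ((0.05 − e)/SE − 1.645).

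| True excess e | SE | Declared non-inferior, as written | Declared non-inferior, conventional |
|---|---|---|---|
| 0 | 0.0201 | 0.002% | 80% |
| 5 points | 0.0221 | 5% | 5% |
| 10 points | 0.0237 | 68% | 0.009% |
| 15 points | 0.0249 | 99% | about 0% |

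Worked example at e = 0.10: as written, Φ(0.05/0.0237 − 1.645) = Φ(0.47) = 68%. The two rules agree only at the margin itself, and one rises where the other falls.

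**3. In observed counts.** Suppose 45/446 (10.1%) are positive in control.

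- The written rule is first met at 85/446 (19.1%) in lesion-only: D̂ = −0.0897, SE = 0.0234, upper limit −0.0511.
- The conventional rule is met up to 52/446 (11.7%): D̂ = −0.0157, SE = 0.0208, lower limit −0.04998.

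**4. Other readings.**

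- If D is taken on HPV-negative proportions, an upper limit below −5 would require lesion-only to be better by more than 5 points. That is superiority by a margin, not non-inferiority.
- If the subtraction is reversed and −5 is kept, the same superiority demand results.
- If only the sign of the margin is changed (upper limit of control minus experimental below +5), the probability is again 80% with equal arms, so the power looks right. At a true 5-point excess it is 99.8%. This would be a false repair.

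**The case against.** The strongest reply is that this is an obvious drafting slip and nobody would apply it literally. The abstract gives the right direction, the sample size fits the conventional rule, and Interim analysis and stopping rules treats excess positivity after lesion-only surgery as harm. The intent is thus recoverable, and a separate analysis plan may state the rule correctly. That is fair as an account of how the error arose. It does not make the sentence right. No other place in the article states the criterion with a confidence limit, and an analysis plan that differed would conflict with it on the primary decision.

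Two narrower points stand:

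- **The interim rule softens the larger figures.** The trial stops if lesion-only positivity exceeds control by more than 15% at the analysis of the first 250 patients. Simulating this with 125 per arm at interim and a 15-point threshold, the trial stops about 14% of the time at a true 10-point excess and about 52% at 15 points. The written rule then declares non-inferiority in about 55% and 48% of trials, not 68% and 99%. The equal-arms and 5-point results hardly change.
- **The abstract is not a serious competing rule.** It mentions no confidence limit, and read alone as a point-estimate criterion it would pass about 50% of trials at a true 5-point excess. But abstracts often omit such detail, and the main text bases inference on the interval. Its main value here is as evidence of intent.

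**Conclusion.** The concern holds. With the contrast as defined, the written condition establishes that lesion-only surgery is worse by more than 5 points, and no alternative reading turns it into a non-inferiority criterion. At the planned size, a trial with truly equal arms would meet it with probability 0.002%, where 80% was intended. A 10-point excess would meet it in about 68% of trials, or about 55% after the interim stopping rule.

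These figures assume 446 evaluable patients per arm, 10% positivity in control and a Wald interval. The direction of the error depends on none of these assumptions. The sample size, margin and alpha are correct for the intended rule. It is most likely a slip, but it must be corrected because it sits in the primary decision criterion.

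**What to change.** Replace the decision sentence in Sample size and statistics with:

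> Non-inferiority is established if the lower limit of the one-sided 95% confidence interval for the difference in HPV-positive proportions (control minus experimental) is greater than −5 percentage points.

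An equivalent form is that the upper limit for experimental minus control is below +5 percentage points. With control minus experimental retained, both the limit and the direction of the inequality must change; changing only the sign of the margin is not enough. Any analysis plan should carry the same sentence. In the abstract, adding the confidence limit and writing percentage points would be a useful but secondary alignment.

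The cost is one sentence, with no extra patients or data and no change to the 892 or the 1000. The article reports recruitment still open in May 2015. The correction should be made and dated before the primary outcome is compared between arms, so that it cannot be taken for a change made after seeing results.
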